## Abstract

**Background:**

Irritable bowel syndrome (IBS) and functional abdominal pain (syndrome) (FAP(S)) are common pediatric disorders, characterized by chronic or recurrent abdominal pain. Treatment is challenging, especially in children with persisting symptoms. Gut-directed hypnotherapy (HT) performed by a therapist has been shown to be effective in these children, but is still unavailable to many children due to costs, a lack of qualified child-hypnotherapists and because it requires a significant investment of time by child and parent(s). Home-based hypnotherapy by means of exercises on CD has been shown effective as well, and has potential benefits, such as lower costs and less time investment. The aim of this randomized controlled trial (RCT) is to compare cost-effectiveness of individual HT performed by a qualified therapist with HT by means of CD recorded self-exercises at home in children with IBS or FAP(S).

**Methods/Design:**

260 children, aged 8-18 years with IBS or FAP(S) according to Rome III criteria are included in this currently conducted RCT with a follow-up period of one year. Children are randomized to either 6 sessions of individual HT given by a qualified therapist over a 3-month period or HT through self-exercises at home with CD for 3 months.

The primary outcome is the proportion of patients in which treatment is successful at the end of treatment and after one year follow-up. Treatment success is defined as at least 50% reduction in both abdominal pain frequency and intensity scores. Secondary outcomes include adequate relief, cost-effectiveness and effects of both therapies on depression and anxiety scores, somatization scores, QoL, pain beliefs and coping strategies.

**Discussion:**

If the effectiveness of home-based HT with CD is comparable to, or only slightly lower, than HT by a therapist, this treatment may become an attractive form of therapy in children with IBS or FAP(S), because of its low costs and direct availability.

**Trial registration:**

Dutch Trial Register number NTR2725 (date of registration: 1 February 2011)

## Background

Irritable bowel syndrome (IBS) and functional abdominal pain (syndrome) (FAP(S)) are functional gastrointestinal disorders (FGIDs) that are characterized by chronic or recurrent abdominal pain in absence of an underlying organic disorder causing the symptoms [1]. These disorders affect approximately 20% of children in Western countries and are also prevalent in Asian countries such as Sri Lanka and China, affecting 12,5 to 20% of school-aged children [2-4]. Altered bowel movements and/or relief of abdominal pain after defecation are present in children with IBS, while defecation pattern is normal in children with FAP(S) [1].

Quality of life (QoL) is significantly impaired in most children with IBS or FAP(S): QoL scores are lower compared to healthy peers and comparable to children with inflammatory bowel diseases [5]. Children with IBS or FAP(S) have an increased risk for anxiety and/or depression and have high rates of school absenteeism [6,7]. Health care costs associated with these FGIDs are considerable. Diagnostic workup for a child with IBS or FAP(S) in the United States costs approximately 6000 dollar. The exact costs of treatment of these children are not known, but are also likely to be significant since treatment of adult patients with IBS costs more than $20 billion per year [8,9].

Pathophysiological mechanisms causing IBS and FAP(S) are not fully clarified to this date, but these FGIDs are thought to be a result of a complex interplay of multiple genetic, psychosocial and physiological factors [10]. Standard medical treatment of IBS and FAP(S) consists of a combination of dietary advice, education and pharmacological therapy, such as pain medication, laxatives, anti-diarrheal medication and antispasmodics [11,12]. Despite these treatments, a significant part of children with IBS or FAP(S) continues to experience symptoms, even into adulthood [13].

In the last 30 years, multiple trials have demonstrated that gut-directed hypnotherapy (HT) is an effective therapy in patients with IBS [14-25]. In gut-directed HT, a hypnotic state is induced and a patient is guided to respond to suggestions towards control and normalization of gut functioning, stress reduction and ego-strengthening [26]. Adult IBS-trials have shown that patients receiving HT report significantly lower levels of abdominal pain and symptom scores compared to patients receiving various control treatments. In addition, these effects of gut-directed HT were shown to be long lasting, up to seven years after treatment [20-22]. Gut-directed HT by a therapist has also been studied in children with IBS or FAP(S) and, in accordance with results of adult studies, these trials show HT to be highly effective compared to standard care [23-25] with persisting positive effects after a period of approximately five years [27]. Although these trials show that gut-directed HT is a valuable therapeutic option, especially in children with persisting symptoms, it is still unavailable to many children with IBS or FAP(S), because gut-directed HT performed by a therapist is costly and frequently not reimbursed by health insurance companies. In addition, the number of well-trained child-hypnotherapists is very limited in most countries and the treatment requires a significant investment of both children and parent(s), since visits to the hypnotherapist may cause work and school absences. Van Tilburg et al. studied the efficacy of home-based HT using self-exercises on compact disc (CD) and showed that approximately two thirds of children receiving this home based treatment responded well with >50% reduction in abdominal pain scores [28]. Potential benefits of this treatment at home include that it is less time consuming and less costly compared to HT with a therapist.

Therefore, the primary aim of this study is to compare efficacy of individual HT performed by a qualified therapist with HT by means of CD recorded self-exercises at home in children with IBS or FAP(S). Secondary aims include adequate relief, the cost-effectiveness, effects on depression and anxiety scores, somatization scores, QoL, pain beliefs and coping strategies.

## Methods/Design

### Study design and population

A randomized controlled trial (RCT) with 1 year follow-up is currently conducted to evaluate the efficacy of individual HT performed by a qualified therapist versus HT at home with self-exercises on CD in children with IBS or FAP(S). This study has been designed in line with the methodological recommendations established by the Rome II consensus on ‘Design of treatment trials for gastrointestinal disorders’ [29]. Nine hospitals throughout the Netherlands participate in this RCT. Children are recruited at the outpatient clinic of the department of pediatric gastroenterology of the academic medical centers in Amsterdam and Maastricht and at the outpatient clinic of the departments of pediatrics of the Medical Center Alkmaar, the Flevo Hospital Almere, the Amphia Hospital Breda, St. Antonius Hospital Nieuwegein, the Maasstad Hospital in Rotterdam, the Maxima Medical Center Veldhoven and the Isala Clinics Zwolle. This RCT has been reviewed and approved by the medical ethics committees of all participating hospitals and has been registered in the Dutch Trial Register number NTR2725. It is granted by the Netherlands Organization for Health Research and Development, ZonMW.

A total of 260 children aged 8-18 years diagnosed with IBS, FAP or FAPS according to the Rome III criteria are included in this RCT [1]. Before inclusion, all patients undergo routine laboratory testing to exclude underlying organic disorders: complete blood cell count, C-reactive protein, alanine transaminase (ALT), aspartate aminotransferase (AST), glutamyltransferase (GGT), creatinine, total bilirubin, amylase, celiac screening (anti-transglutaminase antibodies and IgA), urinalysis, stool parasite analysis and *H pylori* antigens in stool. The need for further diagnostic testing is left to the discretion of the treating physician.

Verbal and written information about the study is given by the pediatrician/pediatric gastroenterologist and patients are asked to participate in this RCT if all criteria are met. Subsequently, verbal and written informed consent is obtained from the child and/or both parents. If the child or parent(s) decide not to participate in this RCT, the reason(s) for not participating are documented, if they want to reveal these.

Inclusion and exclusion criteria

Inclusion criteria

(1) Diagnosis of irritable bowel syndrome (IBS) or functional abdominal pain (syndrome) (FAP(S)) according to Rome III criteria [1]

(2) Age 8-18 years at inclusion

Exclusion criteria

(1) Concomitant organic gastrointestinal disease

(2) Treatment by another health care professional for abdominal pain symptoms

(3) Previous hypnotherapy

(4) Mental retardation

(5) Insufficient knowledge of the Dutch language

After obtaining informed consent, children are randomly allocated using a computerized random-number generator for concealment, to either individual hypnotherapy given by a qualified therapist or home-based therapy with hypnotherapy exercises on CD. Randomization is performed on a 1:1 basis with varying block sizes of 2, 4 and 6. Stratification is based on the including hospital and school level (primary/secondary school).

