### Statistical analysis

Two hundred and sixty children diagnosed with IBS or FAP(S) will be included. The data will be analyzed following the intention to treat principle. The primary analyses will focus on the proportion of patients in both treatment arms in which treatment was successful (>50% reduction abdominal pain frequency and intensity) at T1 and the proportion of patients in which treatment was successful at T3. In addition, abdominal pain levels will be compared in its continuous form using all five moments of measurement during follow-up (after 4 and 8 weeks of treatment, at T1, T2 and T3). These data will be analyzed using linear mixed models to account for correlations of measurements within the same individual. Similar longitudinal, repeated measurement analyses will be performed for the secondary outcomes including depression and anxiety, somatization, health related Qol, pain beliefs, coping strategies and adequate relief. Baseline values will be incorporated in these analyses to adjust for any imbalance at baseline despite randomization and to increase precision by removing between-person variability.

Two explanatory subgroup analyses are planned to evaluate whether there are indications that treatment effects differ between clinical subgroups. Children diagnosed with IBS will be compared to children with FAP(S). Additionally, children in pre-puberty age (13 years or younger) will be compared to older children, since our previous RCT showed that younger children showed a better treatment response up till 6 months after treatment [24].

Economic evaluation will be performed from a societal perspective. Cost-effectiveness and cost-utility ratios will be calculated for the additional costs per extra patient with at least 50% reduction of abdominal pain scores and the additional costs per extra QALY.

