#### Power

The primary analysis focuses on the proportion of patients with at least 50% reduction in abdominal pain levels compared to baseline at the end of therapy and after one year of follow up. Based on previous trials, we made a conservative estimate of this percentage being around 75% in the group receiving HT performed by a therapist. In the group assigned to self-hypnosis with CD, we anticipated this percentage to be marginally lower at 65%. In order to be a reasonable alternative treatment, this percentage should not become lower than 50% in the CD group. This non-inferiority margin should be viewed in relation to success rated with standard medical care of around 30-40% in previous trails [23,24,28]. Based on these expected proportions and a non-inferiority margin at 50%, a total of 115 patients per group are needed to achieve a power of 80% with a one-sided significance level of 5%. Since we expect less than 10% drop-out, our aim is to include 130 patients per group.

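### Randomisation is stratified by hospital and school level, but no analysis the article describes uses these factors; naming them is a cheap improvement of modest size

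*Protocol article*

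**What the plan says.** Study design and population gives the design: "Nine hospitals throughout the Netherlands participate in this RCT", "Randomization is performed on a 1:1 basis with varying block sizes of 2, 4 and 6", and "Stratification is based on the including hospital and school level (primary/secondary school"). Nine hospitals by two school levels make 18 strata.

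Statistical analysis describes the main comparison thus: "The primary analyses will focus on the proportion of patients in both treatment arms in which treatment was successful", at the end of treatment (T1) and at 12 months after it (T3). No test, estimator, model or covariate is named. Linear mixed models for continuous pain, and similar longitudinal analyses for the secondary outcomes, are to allow for correlation within a child. The section then adds: "Baseline values will be incorporated in these analyses to adjust for any imbalance at baseline despite randomization and to increase precision". Hospital and school level are mentioned in none of this.

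The Power section treats the primary endpoint as a comparison of two proportions: 75% success with a therapist, 65% with the CD, a lower limit of 50% for the CD group, 115 per group, 80% power and one-sided 5%.

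**The concern.** Blocked randomisation within strata makes the arms alike on the stratification factors. If those factors predict success, part of the outcome variation can no longer contribute to a chance difference between arms. A plain two-proportion standard error still counts that part. The interval for the risk difference is then too wide, and a test against the margin rejects less often than its nominal level allows.

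The article gives one reason to think school level, which tracks age, is prognostic: "our previous RCT showed that younger children showed a better treatment response up till 6 months after treatment". It gives no between-hospital difference in outcome.

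At stake is some precision in the non-inferiority decision. A home treatment that is in fact acceptable could narrowly fail to be shown so, although the data to sharpen the comparison have already been collected.

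**Working it through.** **Inputs.** From Power: success 0.75 ("we made a conservative estimate of this percentage being around 75% in the group receiving HT performed by a therapist") and 0.65; limit 0.50, that is a margin of 0.75 − 0.50 = 0.25; 115 per group; one-sided 5%. From Study design and population: 9 × 2 = 18 strata; 260/18 = 14.4 children per stratum. The prognostic strength of the strata is not given and is assumed below.

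**1. Reproduce the stated sample size.**
- Variance sum: 0.75 × 0.25 + 0.65 × 0.35 = 0.1875 + 0.2275 = 0.415.
- Distance from the margin: 0.25 − 0.10 = 0.15.
- n = 0.415 × (1.645 + 0.842)² / 0.15² = 114.03, rounded up to 115. This agrees with the plan.
- Power at 115: Φ(0.15/√(0.415/115) − 1.645) = 80.3%.

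**2. Effect of prognostic strata.** Assume that the strata shift the success risk equally in both arms, with a school-level gap d (half the children in each level) and a between-hospital SD s.
- Between-stratum variance: v = d²/4 + s².
- SE used by the unadjusted test: SE_u = √(0.415/115).
- Actual SE under stratified randomisation: SE_t = √((0.415 − 2v)/115).
- Unadjusted power: Φ((0.15 − 1.645 SE_u)/SE_t).
- Stratified power: Φ(0.15/SE_t − 1.645).
- Type I error of the unadjusted test with the CD arm at 0.50 (variance sum 0.1875 + 0.25 = 0.4375): Φ(−1.645 × √(0.4375/(0.4375 − 2v))).

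| Gap d / SD s (points) | SE_t/SE_u | Unadjusted power | Stratified power | n per arm for 80%, stratified (unrounded) | Type I, unadjusted |
|---|---|---|---|---|---|
| 0 / 0 | 1.000 | 80.3% | 80.3% | 114.0 | 5.0% |
| 10 / 5 | 0.988 | 80.6% | 81.1% | 111.3 | 4.8% |
| 20 / 5 | 0.969 | 81.0% | 82.4% | 107.2 | 4.5% |
| 20 / 10 | 0.951 | 81.5% | 83.7% | 103.0 | 4.2% |
| 30 / 10 | 0.918 | 82.3% | 85.9% | 96.2 | 3.7% |

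Worked example, last row: v = 0.0225 + 0.01 = 0.0325, so 0.415 − 2v = 0.35. SE_t = √(0.35/115) = 0.0552 and SE_u = 0.0601. The gain is 85.9 − 82.3 = 3.6 points.

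**3. Simulation check.** The set-up was 18 strata of unequal size, blocks of 2, 4 and 6, 230 children and 6000 trials per scenario. It compared the unadjusted risk difference with a Mantel-Haenszel stratified risk difference (Sato variance).

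| Scenario | Power, unadjusted | Power, stratified | Type I, unadjusted | Type I, stratified |
|---|---|---|---|---|
| 0 / 0 | 80.6% | 80.1% | 5.0% | 5.0% |
| 10 / 5 | 81.0% | 81.3% | 4.4% | 4.7% |
| 20 / 5 | 80.4% | 81.2% | 4.4% | 4.9% |
| 20 / 10 | 81.0% | 83.3% | 4.3% | 5.0% |
| 30 / 10 | 83.3% | 86.4% | 4.2% | 5.5% |

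Monte Carlo error is about √(0.8 × 0.2/6000) = 0.5 points for power and √(0.05 × 0.95/6000) = 0.3 points for type I error. Direction and rough size agree with step 2. In the last scenario some risks were truncated at 99%, so that row is the least reliable.

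**The case against.** The strongest reply is that this is a condensed article. It names no test for the primary endpoint, and covariate lists usually sit in a full protocol or analysis plan, which is not shown. A reader might infer that the trial has decided to compare raw proportions with no adjustment. The text does not say so: it neither excludes the factors nor calls the comparison unadjusted. That part of the reply stands. What remains is that the article does discuss adjustment, states a precision aim, and names only baseline values and within-child correlation. An analyst following it would leave out the factors used to randomise.

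The evidence that the strata matter is also limited:
- The age remark reaches only to 6 months after treatment, whereas T3 is at 12 months. It motivates a subgroup split at 13 years, not an adjustment for school level.
- A reader might count differences between therapists as a hospital effect. Therapists deliver treatment in one arm only, so this is not the common shift in both arms that the calculation assumes.
- No between-hospital difference in outcome is reported.

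If the strata are not prognostic, nothing is lost. Sparse strata also limit what can be gained.

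**Conclusion.** The point holds as a minor, nearly free improvement. The factors that govern randomisation appear in no described analysis. If they are prognostic, an analysis without them is conservative on the risk-difference scale. Over the assumed range the cost is about 0 to 3.6 points of power, with a type I error of about 3.7% to 5%. This rests on stratum effects that are common to both arms and whose sizes are assumed.

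Two stronger readings are not supported. The stated power does not fail: 115 per group gives 80.3% without any adjustment. Nor does leaving out the strata make a false claim of non-inferiority more likely, since the error rate of the unadjusted test is at or below its nominal level.

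**What to change.** State that the primary risk difference and its one-sided 95% limit will be estimated with school level and hospital in the analysis. Two suitable ways:
- a Mantel-Haenszel risk difference stratified by both factors; or
- a logistic model with treatment, school level, hospital and the baseline pain frequency and intensity scores, standardised to a marginal risk difference. The standardisation matters because the margin is on the risk scale, and adjustment does not shrink the standard error of a log odds ratio.

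Add both factors to the mixed models. Give a rule for small sites in advance, either pooling them or fitting hospital as a random effect, because strata average about 14 children. If the factors are to be left out, say why.

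The cost is slightly more analysis work. No new data or patients are needed, since hospital and school level are recorded at randomisation and the pain scores at baseline. The gain may be small where strata are sparse.

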### Interventions

The HT protocol used in this RCT is based on the Manchester protocol for gut-directed HT adapted for children [30] and is comparable to the treatment protocol used in a previous RCT on gut-directed HT in the Netherlands [24]. Hypnotherapy consists of exercises on general relaxation, control of abdominal pain and gut functioning and ego-strengthening suggestions. Several scripts for the exercises used in this RCT are based on scripts used in the van Tilburg et al. trial [28]. Given the nature of HT, blinding of patients and health care professionals involved in the treatment of the participants is not possible.

#### Individual hypnotherapy by a therapist

Individual HT consists of six sessions of 50-60 minutes over a period of three months and is carried out by 11 hypnotherapists affiliated to the recruiting hospitals. All participating hypnotherapists are qualified and have many years of experience in performing HT in children. They have been trained in working with the treatment protocol and instructed to use the same scripts that are used in the CD group, but are allowed to adapt contents and order of these scripts to the child’s interests and specific issues that may come up during therapy. The same protocol is used for children of all ages, but the language used is adapted to the child’s developmental age.

In the first HT session, therapists take a full history. Furthermore, it is explained to both child and parent(s) what hypnotherapy is and how it can help in reducing chronic abdominal pain.

Also, children and parent(s) are instructed not to talk about the pain anymore. In the same session, an exercise on breathing and progressive relaxation is introduced in which children imagine floating on a big cloud. Positive suggestions for decreasing discomfort are given, such as making their hands warm and to place both hands on their belly, imagining the warmth spreading through their abdomen. In the second session, the exercise on progressive relaxation is repeated. Furthermore, an exercise focusing on reduction of anxiety and stress is introduced (‘the favorite place exercise’). In session three, an exercise on ego-strengthening is introduced (‘the rainbow planet exercise’ for children attending primary school; ‘the air balloon exercise’ for children in secondary school). In this hypnosis exercise children choose colors from the rainbow for different needs, for example health, tranquility, courage or confidence. During the fourth session the ‘beach without worries exercise’ is introduced, in which children are encouraged to release stress and again, ego-strengthening suggestions are made. In the fifth session, children do ‘the slide exercise’ in which children visualize sitting on a slide. Suggestions on reduction of anxiety and stress and ego-strengthening suggestions are given as well as visualizations of a well working digestive system with food sliding through the bowel in a comfortable way. In the last session, evaluation of the previous three months will take place. In addition, remaining issues related to the abdominal pain may be addressed and previous exercises are repeated, depending on the needs of the individual patient. Children are advised to keep practicing the HT exercises at home on a regular basis. After the first HT-session all children in the HT-group receive a CD containing standard scripts of all exercises used and they are instructed to listen to the exercises or to practice self-hypnosis on a daily basis. Furthermore, they are encouraged to practice the breathing exercise a few times a day.

